## Abstract

**Background:**

Traditional rural housing in hot, humid regions of sub-Saharan Africa usually consists of single-level, poorly ventilated dwellings. Houses are mostly poorly screened against malaria mosquitoes and limited airflow discourages the use of bednets resulting in high indoor transmission. This study aims to determine whether living in a novel design house with elevated bedrooms and permeable screened walls reduces malaria, respiratory tract infections, and diarrhoea among children in rural Tanzania.

**Methods/study design:**

This is a household-randomized, controlled study in 60 villages in Mtwara, Tanzania. A total of 550 households are randomly selected, 110 of which are allocated a novel design house and 440 households continue to reside in traditional houses. A dynamic cohort of about 1650 children under 13 years will be enrolled and followed for 3 years, approximately 330 living in novel design houses and 1320 in traditional rural houses. The primary endpoint is the incidence of malaria; secondary endpoints are incidences of acute respiratory tract infections and diarrhoea diseases detected by passive and active surveillance. Exposure to malaria vectors will be assessed using light traps in all study houses. Structural, economic, and social science studies will assess the durability, cost-effectiveness, and acceptability of the new houses compared with traditional housing. Environmental data will be collected indoors and outdoors in study homes to assess the differences between house typologies.

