### Study design

This is an open-label, household-cluster, randomized, controlled, superiority trial using a generalized, randomized, complete, block design, with the village as a block. The study arms consist of 110 novel-design houses and 440 traditional African homes.

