#### Participant eligibility

The randomization procedure started by identifying suitable villages based on the eligibility criteria described below.

The following are the village eligibility criteria:Size: a village of about 500 people or more (about 100 households), to make sure that we would have at least five households for randomization.Accessibility: readily accessible throughout the year to assist during the construction phase and surveillance.No competing health interventions: we selected a study area without plans for new, experimental health interventions. The routine government health interventions including the distribution of ITNs continues.No power supply: lack of electricity is representative of most rural Tanzanian villages.No water supply: few rural Tanzanian villages have access to reliable water supplies.

Following the selection of 68 eligible villages, a census of 14,600 households in the 68 villages was conducted, and data on household members and household structures were collected [17]. Data were entered in tablets and subsequently uploaded, stored, and processed using the KoBo Toolbox. Eligible households were selected according to the criteria below.

The following are the household eligibility criteria:There is sufficient land on which to construct another house.At least two children under 13 years old (no lower age limit).Willing to participate in disease surveillance for 3 years.Traditional house design constructed with mud walls, thatched roof, and dirt floor.Householders had access to a pit latrine.No power supply from the grid.No piped water supplied by the municipality.

Eligible households were identified in 60 villages; therefore, participants in 60 out of 68 villages participate in the study.

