### Randomization

All households meeting the eligibility criteria were invited to participate in a randomization process in the form of a village lottery. A total of 862 households were eligible to participate in a lottery to select firstly the 110 new house owners and secondly the 440 households to serve as comparison houses. The lottery was conducted during a public meeting at a central meeting place to which all villagers were invited. All households meeting the inclusion criteria were listed, and cards with the names of the household’s heads were inserted in identical envelopes. The envelopes were placed in a transparent bucket and mixed. The lottery consisted of two rounds where the winning envelope was picked by a literate school child of any age. In the first stage, two envelopes were picked out of the bucket, and the winners were offered a new house. During the second round of the lottery, eight households were randomly selected to participate in the study as comparison households. Comparison households will receive modifications of their homes such as a corrugate iron roof and water harvesting equipment after completion of the 3-year surveillance period. All study families, control and intervention, are enrolled in a health insurance scheme which assures free healthcare for the study duration. Each household meeting the eligibility criteria had an equal and fair chance of being selected to be part of the study (Fig. 2).

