### Community engagement

A hierarchical approach to engage the study population was chosen at the earliest contact with the prospective study communities. The study team sought the advice of the district government and based on their recommendations approached the village leadership to explain the purpose and methods of the proposed study. The village leaders organized village meetings preceding census activities in the villages. Following the completion of the census, all villagers were invited to meetings to explain the purpose of the lottery described above. During the construction phase, there was regular contact with the new house owners and their neighbours. The construction team explained the activities and, where possible, asked the new house owners to participate in the construction.

Following the hand-over of the new houses, the research team realized that envy among community members who had not been allocated a novel design house was hindering study participation. In response, a multipronged community engagement plan was implemented prior to the start of active surveillance activities. A professional drama group developed plays originally meant to be enacted as village theatre. Following COVID-19-related restrictions, the script was transformed into a radio show “Samoe” with 20 episodes of 20 min each, describing the adventures of a young couple after participating in the lottery and winning a new-design home.

Due to the popularity of sports and particularly football, the research team formed a football club which participated in weekly matches in the study villages. Additional sports activities were added for all day village “bonanzas” on weekends. In conjunction with the sports days, village open-air dances were organized in-between and after sports activities. Rest periods between activities are used to introduce the research team and explain the purpose and the methods of the study.

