### Analytical plan

#### Incidence of malaria, respiratory tract infections, and diarrhoea diseases

Protective efficacy against clinical malaria, pneumonia, and diarrhoea diseases will be assessed by comparing incidence rates between the two study arms adopting an intention-to-treat analysis. Children within each household will be monitored using active and passive case detection throughout the study period. After treatment for malaria, the child will not be considered at risk for the following four weeks and this period will be censored. History of travel and nights spent away from the designated household will be captured during weekly surveillance visits and time at risk will be censored for such periods. Initial unadjusted analyses will be based on the comparison of the incidence rates between the two arms. Formal analyses will use a mixed effects Poisson model to test the difference in incidence rate between the two arms allowing for the repeated measurements within a house, a village and the effect of year using of confidence intervals that account for the highest level of clustering [28]. With multiple control and intervention houses within each village, the “intervention*village” interaction will also be quantified. Possible confounders such as age of child, gender, ethnicity, and rainfall will be tested using the mixed effects model. A mixed effects negative binomial model will be considered in case of overdispersion in the mixed effects Poisson model. A comparison of time to infection (both first and repeat) will be examined using a survival analysis approach. Initial analyses will be based on Kaplan-Meier curves with further adjustment for confounders performed using a Cox regression model.

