## Trial status

The random allocation of houses was completed in 2018. The house construction was completed by June 2021. The houses were handed over, and the new residents moved in between June 2021 and January 2021. The disease surveillance started in January 2022. The surveillance will be completed in December 2024. The analysis and publication of the most pertinent findings should be completed by December 2025.

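### Allocation was public and complete in 2018, but the intention-to-treat comparison counts an open cohort of children seen in 2022–2024, with no stated tie to household membership at randomisation

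*Protocol article*

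**What the plan says.** All references are to the protocol article.

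- **Allocation.** Under Randomization: "The lottery was conducted during a public meeting at a central meeting place to which all villagers were invited". Under Trial status: "The random allocation of houses was completed in 2018". The Intervention section puts hand-over of the houses in June 2021, and Trial status puts surveillance from January 2022 to December 2024.
- **Units and cohort.** Study design: "The study arms consist of 110 novel-design houses and 440 traditional African homes". The Abstract describes the children as follows: "A dynamic cohort of about 1650 children under 13 years will be enrolled and followed for 3 years", split as "approximately 330 living in novel design houses and 1320 in traditional rural houses". Clinical data collection covers children under 13 in study households. Under Primary endpoints, the denominator is the time each child lives in the study area.
- **Analysis.** Under the Analytical plan, incidence rates are compared between arms "adopting an intention-to-treat analysis".
- **Pre-lottery record.** Participant eligibility describes a census of 14,600 households in which "data on household members and household structures were collected".
- **Mobility.** Mitigation of bias and confounding, together with the Analytical plan, censors children who move between houses or do not regularly sleep upstairs, and time spent away from the assigned household. Neither section mentions children who come to live in a study household after the lottery.
- **Participation.** Community engagement reports that, after hand-over, "envy among community members who had not been allocated a novel design house was hindering study participation". It adds that an engagement plan was put in place before active surveillance began.

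**The concern.** Randomising households balances the people who lived in them at the draw. It is reasonable to extend that protection to children born to them later. It does not extend to a child who moves in afterwards because the household won a new house with solar light, harvested rainwater and a closed latrine. That entry happens after randomisation and may be caused by the allocation. At least three years separate the lottery from the first surveillance visit, villagers and field staff know who has which house, and the cohort is open.

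Children who moved in or were fostered could differ between arms in previous malaria exposure, carried parasites, nutrition or household circumstances. The covariates the Analytical plan gives as examples (age, gender, ethnicity, rainfall) would not capture most of that. At stake are malaria incidence, annual parasite prevalence and growth, all read as randomised comparisons.

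**Working it through.** **The plan's own figure.** Three children per household gives 110 × 3 = 330 and 440 × 3 = 1320, in total 1650. This matches the Abstract exactly.

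**Share of child-time from children not present at allocation.** The article does not state this share.

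Inputs from the article: allocation at some point in 2018 (month not given, so t₀ runs from 2018.0 to 2019.0), follow-up from 2022.0 to 2025.0, upper age limit 13.

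Inputs assumed: ages uniform over 0–13, exit at 13, and cohort size held constant.

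At time t the share is (t − t₀)/13. Averaged over follow-up it is m = [(2022 − t₀) + (2025 − t₀)] / (2 × 13).

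| Allocation | Start of surveillance | End of surveillance | Average m |
|---|---|---|---|
| Start of 2018 | 4/13 = 30.8% | 7/13 = 53.8% | 5.5/13 = 42.3% |
| Mid-2018 | 3.5/13 = 26.9% | 6.5/13 = 50.0% | 5/13 = 38.5% |
| End of 2018 | 3/13 = 23.1% | 6/13 = 46.2% | 4.5/13 = 34.6% |

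**Relaxing the assumptions** (each range runs from end-2018 to start-2018 allocation):

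- Entry at a fraction f of full replacement gives f·m / (f·m + 1 − m). With f = 0.5: 0.173/(0.173 + 0.654) = 20.9%, up to 0.212/(0.212 + 0.577) = 26.8%.
- 3.5 children per household in 2018 against 3 during follow-up gives 1 − 3.5(1 − m)/3 = 23.7% to 32.7%.
- Enrolment closed in January 2022 with no exit at 13 gives 3/13 to 4/13 = 23.1% to 30.8%.
- More extreme inputs go outside the 20–40% range. With f = 0.25 the share is 11.7–15.5%; with 2.5 children per household in 2018 it is 45.5–51.9%. The 20–40% is therefore a working range and not a bound.

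**When the share exceeds one third.** Setting the f formula equal to 1/3 gives f = (1 − m)/(2m). That is 0.94 for an end-2018 allocation, 0.80 for mid-2018 and 0.68 for the start of 2018.

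**What the share contains.** The age arithmetic does not separate births from children who moved in. The article gives no birth, fostering or migration rate, so the non-birth part cannot be calculated.

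**Illustration of bias from the non-birth part.** All inputs are assumed except the 0.70, which is the 30% reduction in Sample size calculations. Let 15% of novel-arm and 5% of control-arm child-time come from children who moved in.

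- Malaria rate in those children 1.5 times that of residents: 0.70 × (0.85 + 0.15 × 1.5)/(0.95 + 0.05 × 1.5) = 0.70 × 1.075/1.025 = 0.73.
- Malaria rate half that of residents: 0.70 × (0.85 + 0.15 × 0.5)/(0.95 + 0.05 × 0.5) = 0.70 × 0.925/0.975 = 0.66.

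**The case against.** Several points on the other side have force.

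- **The share is not the exposure to bias.** A reader might infer that more than a third of child-time must come from children who joined after allocation, and that the comparison is open to selective joining on that scale. The documents do not support this. The figure needs uniform ages, a constant cohort, exit at 13 and near-full replacement. The article states none of these, and plausible alternatives fall below a third. Most of the share is also likely to be births. This objection stands.
- **No in-migration is documented.** A reader might take the Community engagement passage as evidence that children were drawn into the new houses. It reports reluctance to take part among people without one, which bears on refusal, and it describes a response begun before active surveillance. It shows that allocation affected behaviour and nothing more specific. This stands.
- **Analysing households as allocated is a recognised intention-to-treat approach.** The household is the randomised unit, so an open cohort does not by itself contradict the label. This stands. The difficulty is which children count within the household.
- **Mobile children are already censored.** The rules cover time away from the assigned house. They do not reach a child who moves in permanently and sleeps there as intended, so this answers only part of the point. The confounder list is open-ended, but unmeasured reasons for moving in cannot be adjusted for.
- **The full protocol or the analysis plan may define entry.** That is possible, and a bare absence from an article would be no finding. The point rests on what the article does state: public allocation in 2018, an open cohort from 2022, residence-based person-time and an intention-to-treat label. If an entry rule exists, the action shrinks to stating it.
- **The illustrated bias is modest and its inputs are invented.** Both are true. It shows that the direction is open and does not estimate the size.

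**Conclusion.** The point holds as a weakness in how the analysis set is fixed. The comparison described as intention-to-treat admits children who entered the household after a public allocation, and the article does not separate them from those randomised. Their share of child-time is substantial, roughly 20–40% on plausible inputs and 35–42% with uniform ages and a stable cohort. Those inputs are assumptions.

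The part that can cause bias is narrower: children who joined other than by birth. Its size is unknown and its effect could go either way. Under the assumed figures above, a true ratio of 0.70 would be read as 0.66 to 0.73. This is a risk that should be guarded against, and it is not evidence that the trial's comparison is already biased.

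**What to change.** 1. Link each surveillance child to the pre-lottery census data as far as the records allow. Class the child as (a) listed at census, (b) born since to a listed household member, or (c) joined otherwise.
2. Pre-specify an analysis of malaria and the clinical secondary endpoints restricted to (a) and (b). Preferably this is the primary intention-to-treat set, with the full dynamic cohort as sensitivity analysis. Which set should be primary is open to debate, so at minimum the restricted set should be a named sensitivity analysis.
3. Tabulate joiners, leavers and non-participants by arm and, where possible, by class. The restriction does not correct differential refusal or leaving, and this table is what would reveal them.

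**Cost.** Some linkage work and a few lines of analysis text. The article says member data were collected, but not that they form an individual roster that can be matched to the surveillance identifiers, so linkage may be incomplete. Child-time in class (c) leaves the restricted analysis. Under the assumed 15% and 5%, that is the follow-up of about 0.15 × 330 = 50 and 0.05 × 1320 = 66 children. The real loss depends on the unknown in-migrant share.

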**Discussion:**

This is the first randomized controlled trial to assess the protective efficacy of a new house design targeting malaria in sub-Saharan Africa. The findings of this study could influence the future construction of homes in hot and humid zones of Africa.

**Trial registration:**

ClinicalTrials.govNCT04529434. Registered on August 27, 2020

## Background

The population of Africa, currently around 1.3 billion, is projected to double by 2050 and reach more than 4 billion by 2100 [1]. This population growth will create demand for healthier, more comfortable, and more affordable homes. Sustainable Development Goal 11 proposes adequate, safe, and affordable housing for everyone by 2030 [2]. To achieve this goal, it will be important to know what constitutes a healthy living space.

Traditional rural house construction in hot and humid regions of sub-Saharan Africa often consists of wattle and daub with a thatched roof resulting in single-level, poorly ventilated spaces which can place children at risk of a range of diseases such as malaria, respiratory tract infections, and diarrhoea [3]. Walls constructed of heavy materials with small or absent windows result in an uncomfortable indoor climate that is hot during the night and even hotter during the day. These conditions hamper the use of insecticide-treated nets (ITNs), which further attenuates airflow by a mean of 60% [4, 5]. Compared to elevated bedrooms, single-storey buildings harbour higher mosquito densities [6]. Recently, it has been demonstrated that house entry by malaria mosquitoes can be reduced substantially by elevating the house off the ground [7] and by increasing ventilation to reduce indoor levels of carbon dioxide [8], making it difficult for mosquitoes to locate a blood meal and transmit malaria. Indoor air pollution mostly due to smoke from open fires but also due to dust and allergens from earth floors, muddy walls, and thatched roofs increases the risk of respiratory tract infections [9, 10]. Poor water supply and sanitation predispose to diarrhoeal diseases [11–13].

The novel house design evaluated in this study addresses these environmental health risks. The underlying concept for the design is derived from traditional rural Asian house designs, which are elevated and constructed of light, air-permeable materials that facilitate airflow to minimize contact with vectors [3]. A pilot study of six prototype houses carried out in Magoda, Tanzania, in 2015 found that mosquito entry was reduced by 95% in double-storey buildings and by 70% in screened single-storey buildings compared with unmodified reference houses [14]. Both single- and double-storey houses were 2.3 °C (95% CI 2.2–2.4) cooler compared with traditional houses. The observed reduction in mosquito densities and temperature suggest that double-storey screened houses could protect best against malaria by providing a barrier to mosquito entry and encouraging bednet use in the cooler indoor environment. By promoting airflow and installing chimneys that reduce indoor smoke inhalation, the risk for respiratory tract infections could be reduced. Rainwater collection systems and hygienic, fly-proof latrines could reduce the risk of diarrhoeal disease transmission.

## Study objectives

### Primary objective

The primary clinical objective of the study is to assess over a follow-up period of 3 years whether living in a novel design house will reduce the incidence of malaria in children compared to children living in traditional sub-Saharan African homes.

### Secondary objectives

The secondary clinical objectives of the study are as follows:To determine whether living in novel design houses reduces the incidence of respiratory tract infections in childrenTo determine whether living in novel design houses reduces the incidence of diarrhoea diseases in childrenTo determine whether living in novel design houses reduces *Plasmodium falciparum* parasite rates in childrenTo assess whether living in novel design houses results in improved childhood growth by reducing the incidence of illnessTo determine whether living in novel design houses decreases overall childhood hospitalization ratesTo identify and compare the predominant pathogens causing respiratory tract and diarrhoeal diseases between the study armsTo compare the numbers of malaria mosquitoes and domestic flies entering novel design and traditional housesTo assess the use and acceptability of the novel design housesTo compare the frequency of ITN use is both study armsTo assess the potential cost-effectiveness of the novel design houseTo compare indoor temperature, relative humidity, carbon dioxide, and atmospheric particulate matter with a diameter of less than 2.5 μm (PM_2.5_) concentrations in both study armsTo compare the relative aerosol dispersion rates between the study armsTo assess the durability of the various components of the novel design house

## Methods and study design

### Study area

The study site is in the Mtwara region, on the southeast coast of Tanzania, which shares its southern border with Mozambique. It is an area of forest and scrubland with a very high population-adjusted *P. falciparum* parasite rate standardized to the age group 2–10 years (PAPfPR 2–10 > 30%) [15]. Historically, the climate consists of two rainy seasons: the long rains between February and April and the short rains from late October to December. The lush, green vegetation in the area is replaced by a dry, barren landscape between the rains. Mtwara has an area of 16,710 km^2^ and comprised five districts and nine councils with a population of 1,424,083 people in 2018 [16]. Mtwara region is a leading cashew producer in Tanzania, and more than 90% of its residents are engaged in cashew production, with a small number of fishers [17]. The study will be conducted in 60 villages with households that meet the inclusion criteria of the study (see below) randomly selected from Mtwara’s 110 villages. The study population has no prior experience with health research.

